## 5. Trial Status

Recruitment starts in 2020 and last follow-up is estimated to be completed in 2023.

## Figures and Tables

**Figure 1 audiolres-13-00005-f001:**
[figure not shown]
Overview of study design.

**Table 1 audiolres-13-00005-t001:** Overview of preclinical and clinical DBS studies that applied DBS primarily for tinnitus. We only listed studies that primarily treated tinnitus. GPIAS = gap-prepulse inhibition of the acoustic startle reflex; TFI = Tinnitus Functional Index (clinically significant change, i.e., responder = ≥ 13 point decrease); THI = Tinnitus Handicap Inventory (clinically significant change, i.e., responder = ≥ 20 point decrease).

Animal (Rodent) Studies						
Reference	Design	Target	N	Uni/Bilateral	Stimulation	Outcome
Van Zwieten et al., 2019 [43]	Noise induced tinnitus, within-subject controlled	Dorsal Cochlear Nucleus	10	Bilateral	Continuous stimulation during test	GPIAS, tinnitus behavior was suppressed
Van Zwieten et al., 2018 [47]	Noise induced tinnitus, within-subject controlled	Medial Geniculate Body	11	Bilateral	Continuous stimulation during test	GPIAS, tinnitus behavior was suppressed
Ahsan et al., 2018 [45]	Noise induced tinnitus, within-subject controlled	Dorsal Cochlear Nucleus	9	Bilateral	Continuous stimulation during test	GPIAS, tinnitus behavior was suppressed
Smit et al., 2016 [46]	Noise induced tinnitus, within-subject controlled	Inferior Colliculus	9	Bilateral	Continuous stimulation during test	GPIAS, tinnitus behavior was suppressed
Luo et al., 2012 [44]	Noise induced tinnitus, within-subject controlled	Dorsal Cochlear Nucleus	6	Unilateral	Continuous stimulation during test	GPIAS, tinnitus behavior was suppressed
**Human Studies**						
**Reference**	**Design**	**Target**	**N**	**Uni/bilateral**	**Stimulation**	**Outcome**
Cheung et al., 2019 [24]	Open-label, nonrandomized trial in refractory tinnitus patients	Caudate Nucleus	6	Bilateral	24 weeks open label	TFI (3 responders), THI (4 responders)
Dijkstra et al., 2018 [25]	Case report in refractory tinnitus patients	Ventral anterior limb of the internal capsule & Nucleus Accumbens	1	Bilateral	1 year	TFI (pre = 74, post = 46), THI (pre = 76, post = 32)

**Table 2 audiolres-13-00005-t002:** Eligibility criteria. TQ, Tinnitus Questionnaire; DBS, Deep Brain Stimulation; CI, Cochlear Implant; ABI, Auditory Brainstem Implant.

Inclusion Criteria	Exclusion Criteria
Medically refractory tinnitus * Age 18–69 years Experiencing tinnitus that is non-pulsatile and uni- or bilateral Severe tinnitus (TQ score ≥ 47) Tinnitus, which is chronic (present ≥ two years) and stable (not intermittent ≥ one year) Average pure tone thresholds for 1, 2 and 4 kHz <60 dB for each ear Willingness to participate in the study	Anatomic cause of tinnitus (e.g., vestibular schwannoma, tumor, middle-ear pathology, temporal mandibular disorder) DSM-V psychiatric disorders, other than depression or anxiety disorder Depression or anxiety disorder, manifestation before tinnitus onset Cognitive impairment or coping problems Active otologic diseases Pregnancy or breast-feeding Active suicidal thoughts or recent attempts Life expectancy lower than two years Implantable electronic devices that potentially interfere with DBS (CI, ABI, cortical implant) General contra-indications for MRI or surgery

* Patient does not respond to available tinnitus treatments (e.g., sound enrichment and cognitive behavioral therapy) and is thoroughly evaluated by the multidisciplinary tinnitus team in MUMC+.

**Table 3 audiolres-13-00005-t003:** Schedule of assessments and procedures. T0 is at inclusion. T1 is at the end of the first 6-week treatment period (stimulation ON or OFF). T2 is at the end of the second 6-week treatment period (stimulation OFF or ON). T3 is at the end of the third treatment period of 6 months stimulation ON. MRI, Magnetic Resonance Imaging; CT, Computer Tomography; TFI, Tinnitus Functional Index; VAS, Visual Analogue Scale; ABR, Auditory Brainstem Responses; EEG, Electroencephalography; LFP, Local Field Potentials.

		Inclusion (T0)	Surgery	Recovery	Optimization	Period I (T1)	Washout	Period II (T2)	Washout	Period III (T3)

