## Abstract

Background: Chronic tinnitus can have an immense impact on quality of life. Despite recent treatment advances, many tinnitus patients remain refractory to them. Preclinical and clinical evidence suggests that deep brain stimulation (DBS) is a promising treatment to suppress tinnitus. In rats, it has been shown in multiple regions of the auditory pathway that DBS can have an alleviating effect on tinnitus. The thalamic medial geniculate body (MGB) takes a key position in the tinnitus network, shows pathophysiological hallmarks of tinnitus, and is readily accessible using stereotaxy. Here, a protocol is described to evaluate the safety and test the therapeutic effects of DBS in the MGB in severe tinnitus sufferers. Methods: Bilateral DBS of the MGB will be applied in a future study in six patients with severe and refractory tinnitus. A double-blinded, randomized 2 × 2 crossover design (stimulation ON and OFF) will be applied, followed by a period of six months of open-label follow-up. The primary focus is to assess safety and feasibility (acceptability). Secondary outcomes assess a potential treatment effect and include tinnitus severity measured by the Tinnitus Functional Index (TFI), tinnitus loudness and distress, hearing, cognitive and psychological functions, quality of life, and neurophysiological characteristics. Discussion: This protocol carefully balances risks and benefits and takes ethical considerations into account. This study will explore the safety and feasibility of DBS in severe refractory tinnitus, through extensive assessment of clinical and neurophysiological outcome measures. Additionally, important insights into the underlying mechanism of tinnitus and hearing function might be revealed. Trial registration: ClinicalTrials.gov NCT03976908 (6 June 2019).

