#### 2.4.1. Primary Outcomes

The primary focus of this pilot study is to assess safety and feasibility. Safety will be assessed by reporting the rate and grade of all surgical and stimulation induced adverse events in the study sample during the study period. Feasibility will be assessed in terms of the acceptability of the intervention, by taking qualitative interviews at all major time points (T0, T1, T2, T3; see Table 3), and by comparing satisfaction during sham stimulation and DBS. 

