### 3.2. Stimulation Parameters

Based on the results in rats it is expected that only high-frequency stimulation will be effective for tinnitus reduction [43]. The following stimulation parameters will be used as the minimum and maximum values during the optimization period to determine optimal stimulation parameters: stimulation frequency (2–200 Hz), pulse width (60–450 μs), and voltage (starting from 0 to a maximum of 5 V). Initially, the stimulation will be bilateral with the same parameters on both sides. Voltages will be increased symmetrically depending on the clinical effect and side effects. In case of stimulation induced side effects, bilateral stimulation can be adapted to unilateral stimulation. During treatment, patients will visit the outpatient clinic weekly. During this period, side effects and tolerability of the stimulation in daily life are evaluated; however, no instant change in tinnitus is expected due to the complexity of the disorder and the anticipated burden and duration of tinnitus. Following the treatment episode, there will be a one-week period for washout of a possible residual therapeutic effect. 

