**Visits and Procedures**										
Number of Outpatient visits		2			6	1		1		1
Anesthesiology screening		•								
MRI		•								
CT			•	•						

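### Section 3.2 gives weekly visits and Table 3 one visit per period, so how often the primary safety outcome is ascertained is unsettled

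*Protocol article*

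**What the plan says.** All references are to the protocol article.

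- Section 2.4.1 defines the primary safety outcome as "reporting the rate and grade of all surgical and stimulation induced adverse events in the study sample during the study period".
- Section 3.2 states "During treatment, patients will visit the outpatient clinic weekly", and then "During this period, side effects and tolerability of the stimulation in daily life are evaluated". The paragraph ends: "Following the treatment episode, there will be a one-week period for washout of a possible residual therapeutic effect".
- Table 3, row "Number of Outpatient visits", gives 2 at Inclusion, 6 in Optimization, 1 in Period I, 1 in Period II and 1 in Period III. It places a washout after Period I and another after Period II, and none after Optimization.
- The Table 3 legend gives Periods I and II six weeks each, and for the last period says "T3 is at the end of the third treatment period of 6 months stimulation ON". The abstract describes the same phase as "followed by a period of six months of open-label follow-up".
- Table 3 has no row for adverse events in any phase.

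**The concern.** An adverse-event rate depends on how often patients are asked as well as on how often events happen. Section 3.2 attaches the assessment of side effects to weekly visits, and Table 3 does not show those visits in Periods I, II or III. A reader cannot tell which schedule the primary safety outcome rests on.

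The gap matters most in Period III. This is the first use of stimulation at this target in humans, the Discussion says its stimulation effects are unknown, and most ON exposure is accumulated in these six months. If contact is thin there, mild events that resolve and are never volunteered may go unrecorded. A lower rate in Period III could then be taken for good long-term tolerability when part of it reflects fewer questions.

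**Working it through.** The plan states no figure for contact frequency or event capture, so there is nothing to reproduce. The check is a comparison of the two places, followed by exposure arithmetic.

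**1. Visits implied by each place** (six months taken as 26 weeks)

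| Period | Weeks | Weekly visits, section 3.2 | Table 3 |
|---|---|---|---|
| I | 6 | 6 | 1 |
| II | 6 | 6 | 1 |
| III | 26 | 26 | 1 |

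**2. Which phase the weekly visits belong to**

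- Optimization: supported by the six visits in Table 3. But section 3.2 has the treatment episode followed by a one-week washout, and Table 3 has no washout after Optimization.
- Periods I and II: supported by the washouts. But Table 3 lists one visit in each.
- Period III as well: supported by the legend, which calls it the third treatment period. But Table 3 again lists one visit.

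No reading fits both places completely.

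**3. Share of ON time in Period III**

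Share = W3 / (Wopt + 6 + W3). The 6 is the one ON period among Periods I and II. W3 is 24 to 26 weeks. Wopt is 0 to 6 weeks, an assumption, because the length of Optimization is not given.

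- W3 = 26, Wopt = 6: 26/38 = 68%
- Lowest: W3 = 24, Wopt = 6: 24/36 = 67%
- Highest: W3 = 26, Wopt = 0: 26/32 = 81%

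**4. Contacts per week if Table 3 holds**

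- Optimization: 6/6 = 1.0 (six weeks assumed)
- Periods I and II: 1/6 = 0.17
- Period III: 1/26 = 0.04

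Period III has 1 of the 6 + 1 + 1 + 1 = 9 outpatient visits listed after surgery (11%).

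**5. What under-capture would do (illustration only)**

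Let c be the share of Period III events recorded and s the Period III share of ON time. Assume a constant rate of stimulation-related events during ON time and full capture elsewhere. Then observed/true = 1 − s(1 − c). With s = 26/32 and s = 26/38:

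- c = 1: 1.00
- c = 0.9: 0.92 to 0.93
- c = 0.7: 0.76 to 0.79
- c = 0.5: 0.59 to 0.66

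The documents give no value for c, and c = 1 is not excluded.

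**The case against.** The strongest reply is that the article condenses a fuller protocol. How events are elicited between visits is commonly left to that document, so the missing adverse-event row proves nothing. That stands, and the point does not rest on it. It rests on two statements about visits that the article does make.

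A second reply is that the weekly visits are simply the six in Optimization. This is possible, but the washout sentence does not fit it. It would also leave Periods I to III with the thin contact shown above.

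Two stronger readings are tempting. The documents support neither.

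- A reader might infer that safety in Period III rests on a single recall at T3. Nothing says events are collected only at listed visits. The Discussion requires immediate reporting of serious side effects, and section 3.5 provides for monitoring and periodic safety-board review. Table 3 schedules audiometry, brainstem responses, cognitive tests and psychological questionnaires at T3, so many auditory, cognitive or mood effects still present then could be measured without recall. These provisions do not find mild events that have resolved and were never mentioned. Nor can standard DBS follow-up be assumed to fill the gap, since section 3.1 describes it for after the trial.
- A reader might infer that the event rate must fall by design. That needs incomplete capture, for which no figure exists, and a true decline after Optimization would look the same. The plan also announces no comparison of rates between phases.

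**Conclusion.** Section 3.2 and Table 3 contradict each other on visit frequency, and the assessment of side effects is tied to those visits. If Table 3 is the operative schedule, contact is thinnest (about 0.04 per week) where ON exposure is greatest (about 67% to 81%). Mild, transient, unreported events may then be under-captured in Period III, and rates by phase would not be comparable. The size of any loss cannot be derived from the documents. Serious events, and effects still present at T3, would probably be found.

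The Period I versus Period II comparison is not affected, since both list one visit. The figures assume a 26-week half-year (24 as the lower bound) and an Optimization of at most six weeks. Figure 1 was not available for this check. The point merits correction because safety is a primary outcome of a six-patient first-in-human study, and the remedy is cheap.

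**What to change.** 1. Reconcile section 3.2 with Table 3, stating which phases the weekly visits cover and which phases a washout follows. Which schedule is intended is for the sponsor to say.
2. Ask the same structured adverse-event questions at one common interval in Periods I, II and III, for example by phone. While the blind holds, the caller should be a blinded investigator and not the one who adjusts stimulation.
3. Report events per patient-week by phase, with the number of contacts beside each rate. Do not read a lower Period III rate as better tolerability unless contact intensity is comparable. If Optimization keeps more frequent contact, say so next to its rate.

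Cost: existing staff can make the calls. With a six-week interval, the visits listed for Periods I and II suffice, and Period III needs calls at weeks 6, 12, 18 and 24 before T3: 4 per patient, 24 for six patients. With a three-week interval, it is 1 call in each of Periods I and II and 8 in Period III: 10 per patient, 60 in all. The downside is that more minor events will be recorded.

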**Visits and Procedures**										
Number of Outpatient visits		2			6	1		1		1
Anesthesiology screening		•								
MRI		•								
CT			•	•						
**Outcome Measures**										
Tinnitus severity	TFI	•			•	•		•		•
Tinnitus loudness and burden:	VAS *	•	•		•	•		•		•
Hearing function:	Audiometry ABR	•		•		•		•		•
		•		•		•		•		•
Cognitive functioning **		•				•		•		•
Psychological functioning ***		•				•		•		•
Neurophysiology:	EEG LFP	•		•		•		•		
			•	•						

* Last week of the period, 3 random times per day. ** Cognitive functioning tests include Boston Naming Test, Verbal and letter fluency, 15 Word Test, Trail Making Test and Stroop Color-Word Test. *** Psychological functioning is assessed using 36-Item Short Form Health Survey (SF-36), Beck Depression Inventory II (BDI-II), Beck Anxiety Inventory (BAI), and Hospital Anxiety and Depression Scale (HADS).

## Data Availability

Data can only be viewed by the investigators, IGJ and monitors.

## List of Abbreviations

DBS	Deep brain stimulation
MGB	Medial geniculate body
TFI	Tinnitus Functional Index
VAS	Visual Analogue Scales
MUMC+	Maastricht University Medical Center
TQ	Tinnitus questionnaire
SF-36	36-Item Short Form Health Survey
BDI-II	Beck Depression Inventory II
BAI	Beck Anxiety Inventory
HADS	Hospital Anxiety and Depression Scale
LFP	Local field potentials
CTCM	Clinical Trial Center Maastricht
EDC	Electronic Data Capture
STN	subthalamic nucleus
AC-PC	Anterior Commissure-Posterior Commissure
ANT	Anterior Nucleus of the Thalamus
GPi	Globus Pallidus Internus
